**Fig. 2 Fig2:**
[figure not shown]
Recovery Record for Apple Watch screen examples. Image Action Buttons include icons created and owned by Recovery Record, Inc. ([name], author, CEO). Image Distractions features *Relaxed Corgi GIF* uploaded by GIPHY, 27 June 2016, https://giphy.com/gifs/7Y66VN3rtkPtu. These images were made available for the purpose of this research per our subcontract agreement with Recovery Record, Inc. ([name], Principal Investigator and author). The image titled Distractions features *Relaxed Corgi GIF* uploaded by GIPHY, 27 June. 2016, https://giphy.com/gifs/7Y66VN3rtkPtu. The GIF was accessed utilizing the Recovery Record, Inc. GIPHY account and made available under a license agreement between Recovery Record, Inc. and GIPHY

#### Continuous passive data collection

##### Apple watch

The number and timing of the steps (physical activity) as well as 5-min epoch heart rate are passively collected for each study participant using the Apple Watch and harvested by the *Recovery Record* app using Apple’s Application Program Interface (API). The Apple Watch activates the sensor approximately every 5 min to record heart rate based on 100 Hz using photo plethysmography. Built in signal processing algorithms are used to aggregate measurements to approximately 5-min intervals, a rate consistent with current methodological guidelines (e.g., Berntson [38]). To minimize data loss, these variables are uploaded to the *Recovery Record* server each time the *Recovery Record* app is opened on the iPhone while the Apple Watch is nearby, or at least once per day.

#### Biological sampling

##### Saliva sampling and genotyping

Saliva samples are collected with RUCDR Infinite Biologics saliva collection kits. GWAS profiling will be performed together with additional samples collected by the PGC-ED using the optimal platform at the time of genotyping, most likely a version of the Illumina Global Screening Array (GSA).

##### Fecal sampling and sequencing

In Phase 1, as recipients of a scientific in-kind grant from the now defunct company uBiome, we collected stool samples. ***uBiome*** comprehensively characterized the biogeography of the human microbiome using high-throughput sequencing of the microbial 16S rRNA gene and released all data to UNC for analysis. After their company dissolved in Oct 2019, all processing transferred to the [name] Lab at UNC ([name], Director). In order to obtain high-resolution taxonomic and functional microbiome data, we will perform whole genome shotgun sequencing. Raw sequence data will be quality filtered and trimmed to remove bases with Phred quality scores less than 20. Downstream bioinformatics analysis will consist of: i) taxonomic composition; ii) functional composition; iii) alpha diversity (as measured by absolute numbers of sequence variants and the Shannon index of diversity) and (quantified by Bray Curtis and UniFrac metrics); and iv) computing descriptive statistics and identifying groups within the data, as well as performing statistical analyses between subgroups using additional metadata, where available [39]. Since the sequencing technology and bioinformatics tools are rapidly advancing, we will utilize the most suitable methods and tools available at the time of analysis.

### Planned data analysis

#### Genomics and microbiota aims

We will combine BEGIN samples with other samples in the PGC-ED for meta-analysis. We will conduct cross-disorder analyses to identify loci that cut across diagnostic categories by leveraging existing high-quality results for anorexia nervosa, major depressive disorder, schizophrenia, bipolar disorder, and other psychiatric and metabolic phenotypes. We will use advanced methods [40] to compute SNP heritabilities and genetic correlations across psychiatric and metabolic traits. We will calculate metabolic and psychiatric trait & disorder polygenic scores (PGS) using PRSice, (http://www.prsice.info). A leave-one-sample-out process will be carried out to calculate BN/BED PGSs. The calculated PGS will be the weighted numbers of risk alleles carried by each case and control. This aim will illuminate, from a fundamental perspective, the genetic architecture of BN/BED and its relation to other psychiatric disorders and metabolic conditions.

We will compare taxonomic composition and diversity of the gut microbiota for BEGIN participants, compare BN with BED, and both to a reference control panel. We will control for multiple covariates in all analyses (e.g., obesity).

We can now rapidly do GWAS on multiple phenotypes – e.g., GWAS for 22 K transcriptomic, 8 K proteomic, or 1 K metabolomic measures. (1) We will adapt and extend these methods to evaluate host genomic-microbiota interactions by conducting ~ 15 K GWAS for species-level microbial measures while controlling for multiple comparisons. (2) We will generate microbiome “modules”, clusters of species with high intra-group correlations and low inter-group correlations. We will then do a GWAS for these modules. (3) For all analyses, we will pay particular attention to the genomic regions highlighted in the prior literature (e.g., MHC, autoimmunity, gut barrier, inflammatory bowel disease). (4) We will utilize publicly available databases of summary statistics across a range of psychiatric, personality, metabolic, and physical activity phenotypes and employ both trait-specific polygenic scores (PGS) and multi-polygenic scores (MPS) to predict outcomes. We will use a novel MPS approach developed by collaborator [name] and colleagues [41], that exploits genetic correlations between the outcome trait and a multitude of traits by using the joint predictive power of multiple polygenic scores in one regression model. We will select relevant GWAS from a centralized repository of summary statistics to predict BN, BED, severity, treatment outcome. Using repeated cross-validation, we will train and validate the prediction models using elastic net regularized regression, which is a multiple regression model suited to deal with a large number of correlated predictors while preventing overfitting [42]. We will then add microbiota and phenotyping variables into the model to improve predictive accuracy.

#### Digital longitudinal phenotyping aims

Our dynamic systems approach capitalizes on a combination of the passive and active data collection to address all three of the longitudinal phenotyping aims. Each stable state can be thought of as having homeostatic properties that are reflected in associations between different levels of derivatives (i.e., change in value with respect to time). For example, the relationship between changes in heart rate from one moment to the next and values of heart rate at the previous moment characterize how heart rate fluctuates homeostatically about a “set point.” This set point represents the heart rate value to which the individual’s body returns when the person is at rest [43]. Not only does this association characterize the homeostatic heart rate value itself but also the rate of return to the set point when a person’s heart rate is perturbed (i.e., experiencing distress prior to a binge/purge episode, physical load creating during exercise, etc.). Higher order derivatives and accounting for more variables simultaneously allows for testing more complex homeostatic patterns (e.g., cycles), while including this concept of rate of return to set point (i.e., systemic stability).

Aim 2 will be tested by first depicting the dynamics that lead up to a binge or purge event in a multilevel model. Aim 3 will be addressed by depicting the dynamics once a binge or purge event has occurred. In this case, analyses will focus on the 2 h after binge/purge events (but not within an hour of a future event), again modeling changes in heart rate and steps as a function of current levels in heart rate and steps. Aim 4 will require depicting each instance in time in terms of risk for being in one of the temporal states associated with subsequent binge eating and/or purging. To do so, we will utilize the posterior probabilities from a latent mixture model where each pattern is differentiated by associations amongst different levels of change. Mixture modeling is a taxonomic approach where timepoints within and between individuals can be grouped together as a function of a model. In this case, the model will differentiate groups of data as a function of the dynamic properties.

To help ensure reproducibility, the sample will be split in half with each half used as confirmation on the other half generating competing models. Under large data circumstances such as these, rather than power, the primary concern is a combination of overfitting and gaining a proper gauge of an effect. Generating competing models allows each of the samples to function as confirmation of the other with the better fitting model on both samples providing the more generalizable solution.

## Discussion

As a multi-pronged investigation, BEGIN will have broad impact across various dimensions in the eating disorders field. First, in the biological domain, BEGIN will allow us to identify genetic and gut microbiota contributors to disorder risk and maintenance and identify genomic, enteric microbes, and behavioral predictors of outcome. Second, in the behavioral domain, BEGIN will allow us to build algorithms that predict behavioral events (e.g., impending binges or purges) to enable real-time intervention via wearable technology.

We intend this to be a transformative study in the field of eating disorders. Through deep longitudinal phenotyping via the Apple Watch, we designed BEGIN to rapidly accelerate progress toward personalized precision medicine for BN and BED. Advances in eating disorders treatment have been slow and incremental. In our Agency for Healthcare Quality and Research review of treatments for BED [44], we noted that the evidence base was challenged by small samples and single studies introducing small variations on core therapeutic approaches with little or no additive efficacy. Wearable sensors, such as the Apple Watch with the adapted *Recovery Record* app, offer us the opportunity to develop a transformative improvement in BN and BED treatment. BN and BED are model disorders with discrete and measurable pathognomonic unhealthy behaviors. By applying dynamical systems models to the passive and active data that we collect, we will bypass historical one-size-fits-all CBT interventions for BN and BED and immediately enter the era of personalized interventions for eating disorders. Not only will we be able to build models that predict binge and purge episodes within the acute phase of the illness, but personalized extensions of these models will allow us to identify and alert individuals to impending slips and relapses after recovery.

Although traditional CBT interventions that rely on in-session retrospective recall will never be entirely obsolete, we expect that the just-in-time approach afforded by our dynamical systems models will render ours a central feature in the future treatment of BN/BED. Results from BEGIN will set the stage for subsequent studies in which we will have achieved the ability to discriminate across types of events (e.g., exercise, meal, binge, purge) that will allow us to build in accurate push notifications when an individual’s passive and active data signal an impending binge or purge—truly tailoring treatment and delivering it in-the-moment. Moreover, *Recovery Record* already has a clinician interface, and we predict that we will be able to incorporate our models into provider interfaces such that clinicians will be able to view and interact with the alerts that emerge, thus supporting the provision of data-informed care.

Ultimately, we foresee that this study will advance both cognitive-behavioral approaches to understanding and treating eating disorders and dynamical systems theory of behavior change to incorporate both intensive longitudinal behavioral and physiological data. Although our focus is on eating disorders, we intend our models to be readily adaptable for other psychiatric (and somatic) conditions that have identifiable measurable indices in order to usher us more rapidly toward individualized interventions that attend to the psychology, the biology, and the dynamic environment of the individual.

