## Background

Bulimia nervosa (BN: lifetime prevalence of 1.5% in women and 0.5% in men) and binge-eating disorder (BED: lifetime prevalence of 3.5% in women and 2% in men) are common debilitating eating disorders [1]. BN is marked by uncontrollable eating episodes coupled with compensatory behaviors, whereas BED includes similarly defined binge episodes only in the absence of regular compensatory behaviors. Both disorders are highly heritable (41–82% [2–7]), carry high psychiatric and somatic comorbidity, and have high medication and healthcare utilization, whether or not comorbid obesity is present [8–11]. Suicide risk is significantly elevated in both disorders [12].

The Binge Eating Genetics Initiative (BEGIN) is a multipronged research study that 1) examines the interplay of genomic, gut microbiota, and behavioral factors to explore etiology and develop predictors of risk, course of illness, and response to treatment in BN and BED; and 2) optimizes the richness and longitudinal structure of deep passive and active phenotypic data to lay the foundation for a personalized precision medicine approach enabling just-in-time interventions that will allow individuals to disrupt eating disorder behaviors in real time before they occur.

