### Participants

We are recruiting 1000 individuals with BN or BED.

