### Inclusion criteria

Currently meets Diagnostic and Statistical Manual for Mental Disorders -5th Edition (DSM-5 [27]) criteria for BN or BED (confirmed via validated questionnaire in screening instrument—see Measures)Resident of USAll sexesAge 18–45 yearsReads, speaks EnglishExisting iPhone user with iPhone 5 or laterWilling/able to wear Apple Watch for entire study periodWilling/able to use *Recovery Record* for the entire study periodProvides informed consent to have activity and self-reported *Recovery Record* data harvestedAmbulatory.

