### Procedure

Informed consent is obtained digitally via the *Recovery Record* app. Participants complete an eating disorders diagnostic questionnaire. Those who screen case positive and meet all inclusion criteria are offered the opportunity to participate in the full study (with a second digital informed consent). All responses to questionnaires are encrypted and sent to a secure research server at the UNC Sheps Center for Health Services Research using secure transfer methodologies, who compile and house the data in servers specifically designed for Protected Health Information. Data are de-identified (Sheps Center maintains the key to match records). Study data from *Recovery Record* and the Apple Watch are maintained by *Recovery Record* and only includes passive and active sources necessary for analyses, minimizing exposure of protected health information. To ensure that a high level of security is maintained, data transfer from *Recovery Record* occurs with end-to-end encryption and authentication protocols. Records are only identified with a second study number that can be linked using the data from the Sheps Center. Eligible participants are mailed a package containing a description of the study, saliva collection kit, microbiome collection kit, and an Apple Watch. Saliva kits are returned directly to RUCDR Infinite Biologics where they are stored awaiting DNA extraction and genotyping. In Phase 1, participants returned microbiome kits to uBiome for sequencing; in Phase 2, kits are returned to the [name] lab. Barcodes ensure accurate identification and coordination with phenotypic data. After enrollment and completion of the baseline survey, participants use the Apple Watches and *Recovery Record* for 30 days and complete midpoint and end-of-study surveys at 14 days and 30 days post-enrollment, respectively, to track progress of eating disorder pathology, including binge eating and purging behaviors.

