#### Stratified sampled intensive measurements

##### Daily mood and meal records

These data are collected inside the *Recovery Record* iPhone app that primarily targets adherence to meal monitoring tasks. Participants are prompted with a push notification six times per day corresponding to meal and snack times to complete an evidence-based CBT-style question set (what was eaten, with whom, where, and what behaviors were used) in addition to optional symptom-focused questions including current emotional state, urges to engage in eating disorder behaviors, sleeping patterns, hunger levels, gastrointestinal problems, and intrusive thoughts.

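### Stool taken from current cases can show microbiota associated with BN/BED, but not microbial contributors to disorder risk

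*Protocol article*

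**What the plan says.** Three parts of the protocol article bear on this.

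- **The inference.** The Discussion says "BEGIN will allow us to identify genetic and gut microbiota contributors to disorder risk and maintenance". The Background describes a study that "examines the interplay of genomic, gut microbiota, and behavioral factors to explore etiology and develop predictors of risk".
- **The sample.** Under Participants: "We are recruiting 1000 individuals with BN or BED". The first inclusion criterion is "Currently meets Diagnostic and Statistical Manual for Mental Disorders -5th Edition (DSM-5 [27]) criteria for BN or BED". Stool comes from a kit sent after eligibility is established (Procedure): "Eligible participants are mailed a package containing a description of the study, saliva collection kit, microbiome collection kit, and an Apple Watch". Follow-up is the 30 days after enrollment.
- **The comparison.** Under Genomics and microbiota aims, the plan is to "compare BN with BED, and both to a reference control panel". Covariate adjustment is promised with an open list in which obesity is the one example.

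The article also collects relevant behavioral data. The EDE-Q is given at baseline, midpoint and endpoint. Prompted meal records ask "what was eaten, with whom, where, and what behaviors were used". Binge and purge episodes are logged through the watch.

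**The concern.** Genotype and stool are placed under one causal word, contributors, although they stand in different relations to onset. Germline genotype is present before the illness. Stool composition is measured during it, in people who are bingeing and, in BN, compensating.

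The Background defines BN by binge episodes with compensatory behaviors, and BED by binge episodes without regular compensation. Compensation therefore tracks the BN–BED contrast, and bingeing tracks the contrast with controls. A microbial feature that differs could have preceded the disorder, could result from it, or both.

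At stake is the reading of the microbiota results. A consequence of the behavior could be reported as a contributor to risk and carried into the search for drug targets that the Intestinal microbiota section has in view. The article plans to share its data widely, so others could repeat that reading.

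**Working it through.** The article gives no figure on this point and none needs recomputing. The check is whether the design can support the wording.

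1. **Timing.** A contributor to risk has to act before onset. Every recruited participant is a current case, and the kit is mailed only after eligibility. The article describes no at-risk, pre-onset or recovered group. All stool from recruited participants is therefore post-onset, however many samples each person gives.

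2. **Contrasts.** BN against BED compares two ill groups and does not bear on the risk of becoming ill. Cases against a reference panel compares ill people with others at a time when the defining behavior is already under way.

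3. **Adjustment.** Let M be a microbial feature, B the recent behavior and D the diagnosis. Take two simple orders.
   - M → B → D: the microbe promotes the behavior, and the behavior defines the diagnosis.
   - M ← B → D: the behavior alters the microbe and also defines the diagnosis.

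   In both, M and D are associated when B is ignored, and M is independent of D given B. Adjusting for B gives the same answer under a true contribution as under a pure consequence. Against controls there is a further difficulty: B is part of the definition of D, so the two can hardly be varied separately.

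4. **Sample size.** Recruiting 1000 people narrows random error. It does not make the two orders in step 3 distinguishable.

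5. **Other planned steps.** The elastic-net model adds microbiota and phenotype to improve prediction, which does not establish direction. The planned GWAS of roughly 15 K species-level microbial measures might lend host-genetic support to some features, but the article does not describe using it to order cause and effect.

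6. **Parts of the claim not affected.** Genetic contributors are outside the problem. Maintenance and outcome prediction are less exposed: microbiota during illness is relevant to both, and there are 30 days of follow-up.

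**The case against.** The strongest reply is that this is one sentence in a Discussion. The working plan is mostly associational or predictive: it characterizes the microbiome, compares groups and builds predictive algorithms. A predictor need not be a cause. This stands in part, and it is why the remedy is mainly wording. But the sentence is unqualified and the Background also ties microbiota to etiology and risk. A predictor of risk, even a non-causal one, has to be measured before the outcome it predicts.

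A second reply is that covariates are covered: "We will control for multiple covariates in all analyses (e.g., obesity" leaves the list open, subgroup analyses using additional metadata are planned, and the complete list may sit in a fuller document. That is right as far as it goes. A reader might infer that the plan ignores recent behavior; the article does not support that, and an incomplete covariate list in an article is not a fault. The point survives because no covariate list settles direction.

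A reader might also infer that each person gives a single stool sample. The article describes one mailed kit, but does not state the number of samples or the collection day, and the sampling-flow figure is not shown. The argument does not depend on it.

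Finally, that bingeing, purging or diet alters stool is not established in the article. The argument needs only that it is a live possibility. The article itself excludes antibiotics or probiotics in the preceding 30 days on account of fecal sampling, so it accepts that recent exposures can matter.

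**Conclusion.** The concern holds for one claim: that the study will identify gut microbiota contributors to disorder risk. The described design supports association with current BN/BED. It does not support a statement about what preceded the disorder.

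This rests on two things: the sampling and comparison groups are as the article describes them, and reverse causation is plausible.

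Its size is qualitative. It is tempting to attach a probability of a false lead, but the article gives no effect of behavior on stool, no BN/BED split and no size for the reference panel. Any such number would only be the power to detect an assumed shift and would say nothing about how likely that shift is. No planned analysis is shown to be wrong; what changes is the conclusion that may be drawn from it.

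**What to change.** - **Wording.** In the Discussion, and wherever microbiota results are tied to risk or etiology, describe them as associated with current BN/BED. State that these comparisons cannot separate cause from consequence. The genetic part of the sentence can stay.
- **Sensitivity analysis within cases.** Relate each BN/BED-linked microbial feature to baseline EDE-Q binge and purge frequency. Where the stool date falls after app and watch logging began, also relate it to the logged meals and binge and purge events. The kit and the watch arrive in the same package, so some stool may come before any logging; for those people the baseline EDE-Q is the available measure.
- **Reporting.** Present this as descriptive, not as a filter for causal claims. A microbe that promotes bingeing would also correlate with binge frequency, so discarding features that follow recent behavior could discard true contributors. For a similar reason, restricting the BN group by recent behavior is not advised: it conditions on part of the diagnosis.

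The cost is a more modest claim and a little more analysis. The behavioral data are already planned; the logged-data part also needs the stool date, which may already be recorded.
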